## Abstract

**Background:**

Postoperative surgical site infections cause substantial morbidity, prolonged hospitalization, costs and even mortality, and remain one of the most frequent surgical complications. In prospective trials with adequate follow-up, more than 20 % of patients undergoing elective colorectal surgery are affected and methods to reduce surgical site infections are urgently needed. Negative-pressure incision therapy is a novel intervention that holds promise to reduce postoperative wound infection rates, but has not yet been rigorously tested in a randomized controlled trial.

**Methods/Design:**

The aim is to investigate whether the postoperative application of a negative-pressure incision therapy device for 5–7 days reduces the rate of surgical site infections following open elective colorectal surgery by 50 %. This is a randomized, controlled, observer-blinded multicentre clinical trial with two parallel study groups. The primary outcome measure will be the rate of surgical site infections within 30 days postoperatively. Surgical site infections are defined according to criteria of the US Centers for Disease Control and Prevention. Statistical analysis of the primary endpoint measure will be based on the intention-to-treat population. The global level of significance is set at 5 % (two-sided) and the sample size (*n* = 170 per group) is determined to assure a power of 80 %.

**Discussion:**

The Poniy trial will explore whether the rate of surgical site infections can be reduced by the application of a negative-pressure incision therapy device in patients undergoing open elective colorectal surgery. Its pragmatic design guarantees high external validity and clinical relevance.

**Trial registration:**

Deutsches Register Klinischer Studien DRKS00006199.

## Background

### Rationale

Postoperative surgical site infections are one of the most frequent surgical complications and a major cause of postoperative morbidity, prolongation of hospital stay, health care costs and even mortality. An estimated 300,000–500,000 surgical site infections occur in the USA annually [1–4]. In Germany, approximately 60,000–200,000 surgical site infections following surgical interventions are reported every year [5–8].

Despite the implementation of such preventive measures as preoperative antibiotic prophylaxis [9–11] and antiseptic skin cleansing [9, 12], surgical site infection rates in prospective trials using the standardized criteria of the US Centers for Disease Control and Prevention (CDC) remain above 15 % after general abdominal surgery [13–16]. In patients undergoing colorectal surgery, surgical site infection rates as high as 20 % and up to 32 % are reported from randomized controlled trials [14, 15, 17, 18]. National data from the USA support these numbers [19].

Several studies have shown an increase in the mean length of hospital stay by 6 to 24 days if surgical site infections occur [4, 20–23]. The resulting direct costs have to be added to indirect costs such as loss of workforce or insurance payments resulting in substantial expenses for the health care system [24–26].

The most frequent pathogens causing postoperative surgical site infection in colorectal surgery are endogenous pathogens from the patient’s gastrointestinal tract [7, 9]. A significant number of surgical site infections occur after postoperative day 5 [14] and it is was proposed that clearing contaminated secretions from the wound might reduce the incidence of surgical site infection [27]. Negative-pressure incision therapy (NPIT) devices were designed to remove fluids from the incisional wound in the early postoperative phase, to reduce tensile forces across the incision and to protect the incision from external contamination. While positive results have been shown *in vitro* and in animal models, the benefit of NPIT devices in clinical practice remains largely unclear.

### Previous trials

Several previous trials have investigated the effect of NPIT in a variety of settings; however, all trials exhibit considerable risk of bias. Stannard *et al.* [28] compared an NPIT system against standard dressings in a single-centre randomized controlled trial in patients with haematoma or fractures following high-energy trauma. In 44 patients with traumatic haematomas, the duration of wound drainage as well as the rate of surgical site infection was reduced using the NPIT system (surgical site infection rates were reduced by 50 % from 16 % to 8 %). The same authors reported a randomized single-centre study in 117 patients with open traumatic fractures randomized to irrigation and debridement followed by standard fine mesh gauze dressing compared with the same procedure followed by NPIT [29]. The authors reported significantly less infections in the NPIT group (7 versus 2; *P* = 0.024).

Gomoll *et al.* [30] reported a case series of 35 patients treated with an NPIT system following foot and ankle trauma and found no surgical site infection in NPIT-treated patients. Similarly, Reddix *et al.* [31] found no surgical site infections in a case series of 19 morbidly obese patients undergoing acetabular fracture repair followed by NPIT therapy. In a second retrospective series by the same authors [32], 66 patients undergoing acetabular repair followed by standard dressings were compared with 235 patients with acetabular repair followed by NPIT therapy. While the control group exhibited 6.1 % deep wound infections, only 1.3 % in the NPIT group showed deep wound infections.

Atkins *et al.* [33] and Colli *et al.* [27] reported a case series with a total of 67 patients using an NPIT system following cardiac surgery on sternal wounds. NPIT therapy was well tolerated and might have prevented surgical site infections in these cases.

Matatov *et al.* [34] used an NPIT system on groin wounds following vascular surgery. While surgical site infections were observed in 30 % of patients in the control group, only 6 % of wounds were infected in the NPIT group. Similar results were reported in a small single-centre trial with 50 patients (25 per group) undergoing colorectal surgery [35]. In this population, NPIT reduced infectious wound complications from 11 cases to 2 (*P* = 0.008).

A recent Cochrane review [36] evaluated NPIT therapy for skin grafts and surgical wound healing by primary intention in regard to the proportion of surgical wounds that healed completely. The review concluded that very limited evidence exists to evaluate NPIT and concluded that high-quality trials in this field are urgently needed.

Current data show that NPIT therapy can be used with few adverse events on different types of wound; however, a multicentre, high-quality randomized controlled trial evaluating NPIT therapy in abdominal surgery has not yet been performed.

### Objective

The Poniy trial aims to investigate whether the application of an NPIT device (Prevena Incision Management System, KCI, Inc., San Antonio, TX, USA) reduces the rate of surgical site infections within 30 days postoperatively, in surgical patients who underwent elective open colorectal surgery, by 50 % (from 25 % to 12.5 %). This rate of reduction is assumed based on previous studies with the NPIT device, all of which showed a reduction of at least 50 % [28, 29, 32, 34, 35]. A number of secondary outcome parameters have been defined as secondary endpoint measures to further evaluate the efficacy of the NPIT system in abdominal surgery (see section outcome measures).

## Methods/Design

### Trial sites

The Poniy trial will be performed at 15 sites of the Trial Network (CHIR-Net) of the German Surgical Society (Deutsche Gesellschaft für Chirurgie). Most of these sites have participated in previous randomized controlled trials and all centres were adequately trained and prepared according to the ICH-GCP (International Conference on Harmonisation of Technical Requirements for Registration of Pharmaceuticals for Human Use—Good Clinical Practice) rules for participation in this trial.

### Trial population and eligibility criteria

All adult (≥18 years of age) surgical patients scheduled for elective open colorectal surgery will be eligible, if they are able to understand the extent and nature of the Poniy trial and if they provide written informed consent. The following exclusion criteria were defined: (a) pregnant or breast-feeding women; (b) open abdominal surgery within the 60 days immediately prior to the trial operation; (c) planned relaparotomy within 30 days after trial operation; (d) laparoscopic or laparoscopic assisted abdominal operations; (e) patients that received preoperative antibiotic treatment.

### Sample size

A total of 152 patients will be analyzed per group. Given an estimated drop-out rate of approximately 10 %, 340 patients will be randomized to the two treatment arms.

### Type of trial

This is a randomized, controlled, observer-blinded multicentre surgical trial with two parallel study groups.

### Recruitment and trial timeline

Fifteen centres of general and abdominal surgery in Germany will participate in this trial. The centres include university hospitals and community hospitals, some of which are certified centres for colorectal surgery (Darmkrebszentrum, German Cancer Society, DKG). All centres are members of the Trial Network (CHIR-Net) of the German Surgical Society. Physicians or nurses involved in the trial have been trained in ICH-GCP prior to initiation of the trial. Informed consent will be obtained from each patient. Furthermore, all centres and participants were specifically instructed in study-specific procedures before the start of the trial. The centres will be supported by an ICH-GCP qualified flying study nurse from the CHIR-Net Surgical Regional Centre in Munich to ensure protocol conforming data acquisition and trial interventions. Stratification will be performed according to centre.

The duration of the recruitment phase is expected to be 14 months. The last follow-up will be performed a maximum of 30 days after the last patient undergoes the trial intervention. Hence, the total duration of the trial (first patient in to last patient out) is expected to be 15 months. The study flow is outlined in Fig. 1.

**Fig. 1 Fig1:**
[figure not shown]
Flow chart of the Poniy trial. NPIT, negative-pressure incision therapy; postOP day, postoperative day; R, randomization

### Randomization and blinding

Randomization and blinding will be performed with the help of sealed, opaque, individually numbered envelopes, restricted to choosing one at a time. The envelopes contain data sheets with information regarding the group allocation and the randomization number. Both are prefabricated by a biostatistician of the *Technische Universität München* (Munich, Germany). Randomization (visit 2, see Fig. 1) will be performed in the operation theatre at the end of surgery, after closure of the skin. This prevents potential bias by different methods of wound closure or wound irrigation. An interrupted skin closure must be performed with either sutures or staplers, according to local practice.

Randomization will be stratified by centre. To assure balanced group sizes, a block-wise randomization will be applied. Basic characteristics of the patient and day of randomization must be documented on the randomization sheets. Subsequently, randomization sheets must be dated, signed and stored away from the patient records and the trial documents, as well as the investigator site file, to ensure blinding. Patients, outcome assessors and the trial statistician will be blinded for the trial intervention. The outcome assessor (postoperative surgical site infection) will therefore neither be part of the surgical team that performs the trial intervention nor take part in the postoperative care of the patient and will have no access to the randomization sheets. Blinding of patients is not feasible, as the NPIT wound dressing system is different from the standard sterile dressing. However, the primary endpoint measure (whether or not there is surgical site infection according to the CDC definition, Table 1) cannot be influenced by the subjective assessment of the patient.

**Table 1 Tab1:** Definitions of abdominal surgical site infections classified according to the Centres for Disease Control and Prevention [9]

Superficial incisional surgical site infections	Deep incisional surgical site infections^a^	Organ or space surgical site infections
1. Infection occurs within 30 days after the operation, and	1. Infection occurs within 30 days after the operation, and	1. Infection occurs within 30 after the operation, and
2. Infection involves only skin or subcutaneous tissue of the incision, and	2. Infection involves deep soft tissues (e.g., fascial and muscle layers) of the incision, and	2. Infection involves any part of the anatomy (e.g., organs or spaces), other than the incision, which was opened or manipulated during an operation, and
3. At least one of items A to D	3. At least one of items A to D	3. At least one of items A to D
A. Purulent drainage, with or without laboratory confirmation, from the superficial incision	A. Purulent drainage from the deep incision but not from the organ or space component of the surgical site	A. Purulent drainage from a drain that is placed through a stab wound^b^ into the organ or space
B. Organisms isolated from an aseptically obtained culture of fluid or tissue from the superficial incision	B. A deep incision spontaneously dehisces or is deliberately opened by a surgeon when the patient has at least one of the following signs or symptoms: fever (>38 °C), localized pain, or tenderness, unless site is culture-negative	B. Organisms isolated from an aseptically obtained culture of fluid or tissue in the organ or space
C. At least one of the following signs or symptoms of infection: pain or tenderness, localized swelling, redness, or heat and superficial incision is deliberately opened by surgeon, unless incision is culture-negative	C. An abscess or other evidence of infection involving the deep incision is found on direct examination, during reoperation, or by histopathologic or radiological examination	C. An abscess or other evidence of infection involving the organ or space that is found on direct examination, during reoperation, or by histopathologic or radiological examination
D. Diagnosis of superficial incisional surgical site infections by the surgeon or attending physician	D. Diagnosis of a deep incisional surgical site infection by a surgeon or attending physician	D. Diagnosis of an organ or space surgical site infection by a surgeon or attending physician

^a^Report infection that involves both superficial and deep incision sites as deep incisional surgical site infection; report organ or space surgical site infection that drains through the incision as deep incisional surgical site infection

^b^If the area around a stab wound becomes infected, it is not a surgical site infection; it is considered a skin or soft tissue infection, depending on its depth

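### The envelope rule neither binds number order nor commits the patient before the arm is seen, so picking or swapping is not excluded and the protection claimed for late randomization is conditional

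*Protocol article*

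**What the plan says.** All the rules stand in one section of the protocol article, Randomization and blinding.

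- **Vehicle and rule of use:** "sealed, opaque, individually numbered envelopes, restricted to choosing one at a time". No other restriction on the order of use is given.
- **Contents and preparation:** "The envelopes contain data sheets with information regarding the group allocation and the randomization number"; "Both are prefabricated by a biostatistician".
- **Timing:** randomization is "performed in the operation theatre at the end of surgery, after closure of the skin". The benefit claimed for this is unqualified: "This prevents potential bias by different methods of wound closure or wound irrigation".
- **Link to the patient:** "Basic characteristics of the patient and day of randomization must be documented on the randomization sheets". The sheets are then dated, signed and kept apart from the patient records, the trial documents and the investigator site file.
- **List structure:** "Randomization will be stratified by centre. To assure balanced group sizes, a block-wise randomization will be applied". Block size is not given, which is normal.
- **Visibility:** "Blinding of patients is not feasible, as the NPIT wound dressing system is different from the standard sterile dressing". The same visible difference means that the team fitting the dressing knows every arm once it is assigned.

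**The concern.** Numbering an envelope protects the sequence only if the numbers must be followed. The stated rule speaks of choosing, so a site could take any envelope from its stock and still comply. If the patient is written only on the sheet taken from inside, the arm is seen first and the patient committed second. An unwanted allocation could then be laid aside and another envelope opened.

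At that moment the team knows how the operation went: contamination, irrigation, closure, and the patient's general risk. Those are determinants of the primary endpoint, surgical site infection within 30 days. If allocation depends on them, the comparison carries selection bias of unknown direction. The primary model (Analysis of the primary endpoint measure) includes centre and possible baseline differences, which can address only what was measured.

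**Working it through.** **1. The stated steps in order.**

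| Step | Stated | Not stated |
|---|---|---|
| Take an envelope | One at a time, numbered | That the lowest unused number is taken |
| Before opening | Skin is closed | That the patient is entered on the envelope or a log |
| Open | Sheet shows arm and randomization number | – |
| After opening | Patient characteristics and day on the randomization sheet, then date and signature | – |

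The article calls the enclosed papers data sheets and the completed papers randomization sheets. Reading them as the same paper is the natural reading, but it is an inference.

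**2. What each gap does.** Picking any number from opaque sealed envelopes does not by itself reveal an arm. It can break up the centre's blocks, and it makes an out-of-order number compliant. Late commitment is what allows an opened envelope to be rejected. Together they leave selective use open.

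**3. The timing claim.** Late randomization keeps the arm from influencing closure and irrigation if the arm is unknown while they are done. That condition is not stated. A swap after closure would not change how the wound was closed, but could tie the arm to it.

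**4. Sample size check.** Inputs (Sample size calculation): 25% v 12.5%, two-sided 5%, power 80%, chi-square test. With mean rate 0.1875:

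n = [1.960 × √(2 × 0.1875 × 0.8125) + 0.842 × √(0.25 × 0.75 + 0.125 × 0.875)]² / 0.125² = 151.9, so 152 per group.

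This reproduces the stated figure. Nothing in this point changes it.

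**5. Illustration of stakes (assumed).** No true effect; high-risk patients at 35%, low-risk at 15%, overall 25%. A fraction f of allocations is steered in one direction, so the spurious difference is f × (35 − 15) points. The rejection rate comes from the normal approximation to the chi-square test with 170 per arm.

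| f | Spurious difference | Two-sided rejection rate |
|---|---|---|
| 5% | 1 point | 5.5% |
| 10% | 2 points | 7.1% |
| 20% | 4 points | 13.6% |

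**6. Predictability (assumed).** The centre average is 340/15 = 22.7 patients, or 22.7/14 = 1.6 a month, few enough for a team to remember. If blocks were fixed at size 2m, known to the site and opened in order, a share 1/(m + 1) of allocations would be certain in advance.

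| Block size | Certain | Of 340 | Best guess right |
|---|---|---|---|
| 2 | 50% | 170 | 75% |
| 4 | 33% | 113 | 71% |
| 6 | 25% | 85 | 68% |
| 8 | 20% | 68 | 67% |

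With sizes varied among 4, 6 and 8 the certain share falls to about 2% in a 23-patient centre, even if the possible sizes are known. The article does not say which case applies, so none of these figures describes the documented design.

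**The case against.** The strongest reply is that a condensed article need not print a randomization procedure. The envelopes are opaque, sealed, numbered and prepared by a biostatistician. Centres were instructed in study-specific procedures (Recruitment and trial timeline), and monitoring procedures are left to a manual, with on-site and close-out visits planned (Monitoring). Opening in order and logging may well be current practice. This stands in part: the gap is a risk not excluded, not a breach shown. It does not remove the point, because the article states a rule of use, and that rule permits choice.

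Three stronger readings are tempting and not supported:

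- **That the next arm can be guessed.** This needs fixed, known blocks and opening in sequence. Block size and variation are properly withheld, and sequential opening is exactly what the rule does not require, so block-end prediction and free picking cannot be charged together at full strength.
- **That a swap leaves no trace.** A discarded envelope leaves an unmatched number, and out-of-order use shows when numbers are set against the signed dates. The weakness is only that, under the present wording, an out-of-order number is not a deviation.
- **That late randomization gives no protection.** It gives real protection for closure and irrigation while the arm is unknown. The section also requires interrupted closure, leaving only sutures or staplers to the site.

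That the sites hold the envelopes is likewise an inference, from their use in theatre.

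**Conclusion.** The point holds as a cheap improvement in concealment. The stated rule does not bind number order and, on the natural reading of the sheets, commits the patient only after the arm is seen by an unblinded team. Selective picking or swapping is not excluded, and the unqualified claim for late randomization should be made conditional. This rests on the wording of one section and on the inference that the enclosed sheet and the completed sheet are one paper. No amount of bias is established: the error rates and predictability shares above depend on assumed steering, risk shifts and block designs.

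**What to change.** In Randomization and blinding, replace the restriction quoted from that section with: *Envelopes are sequentially numbered per centre and opened strictly in ascending order. Patient identifier, date, time and signature are written on the sealed envelope before it is opened, and only after skin closure is complete.* Qualify the next claim so that bias from closure and irrigation is said to be avoided provided the next allocation is unknown during closure.

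The cost is a label on each envelope and a few seconds of writing in theatre. Recruitment is planned to start on 1 October 2015, so the wording can be changed before first use. If sites already work this way, only the text needs correcting.

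Two optional additions, neither shown to be absent: undisclosed varied block sizes, which matter more once opening in order is enforced and whose price is slightly looser balance within centres; and reconciliation of opened and unopened envelopes against the list at the visits already planned.

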### Interventions

The schedule of trial interventions is presented in Table 2.

**Table 2 Tab2:** Study visits of the Poniy trial

Activity	Visit 1 (screening, inclusion)	Visit 2 (operation + randomization)	Visit 3 (postoperative day 5–7)	Visit 4 (postoperative day 9–11)	Visit 5 (discharge)	Visit 6 (postoperative day 30–35)	Optional visit (anytime between visits 2 and 6)
Inclusion and exclusion criteria	×						
Informed consent	×						
Medical history	×						
Physical examination	×						
Surgery		×					
Randomization		×					
Documentation of surgical site infection^a^			×^b^	×^b^	×^b^	×^b^	×^b^
Documentation of other wound complications^c^			×				×
Measurement of wound length			×				
Documentation of wound pain (visual analogue scale, 1–10)			×	×	×	×	×
Documentation of reoperation			×	×	×	×	×
Documentation of adverse or serious adverse events		×	×	×	×	×	×
Documentation of antibiotic-therapy			×	×	×	×	×

^a^By blinded wound assessor according to definition of US Centers for Disease Control and Prevention

^b^In case of surgical site infection, a microbiological swab according to local practice should be obtained for microbiological specification and antimicrobial testing

^c^Documented as ‘yes’ if blister formation and ‘no’ otherwise

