### Outcome measures

The primary efficacy endpoint measure of the Poniy trial is the rate of surgical site infections within 30 days after the operation, according to CDC criteria, which constitute an internationally accepted standard definition [9] (Table 1). If the patient’s wound cannot be evaluated on postoperative day 30, a clinical evaluation according to the CDC criteria up to postoperative day 35 will be allowed.

The following outcome measures have been defined as secondary endpoint measures:Duration of hospital stay (in days);Rate of reoperation in both groups;Duration of postoperative antibiotic treatment in both groups within 30 days (in days);Duration of NPIT therapy (in days) in the interventional arm;Wound pain, as assessed by a visual analogue scale (graded from 1 to 10) in both groups;Rate of wound complications other than wound infections in both groups;Number of postoperative severe adverse events in both groups within 30 days.

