### Safety evaluation and reporting of adverse events

An adverse event is defined as any untoward medical occurrence in a patient that does not necessarily have a causal relationship with the trial treatment and that occurs between inclusion of the patient and visit 6. The following exceptions are predefined in the study protocol and will not be recorded as adverse events: (1) occurrence of surgical site infection (the primary endpoint measure) is assessed as endpoint measure only (not as an adverse event); (2) any adverse event that is expected during the postoperative course or the underlying disease (e.g., pain, nausea, vomiting, hypertension, hypotension, imbalances of blood sugar or electrolytes or other laboratory values out of range) and that does not exceed grade I of the Dindo–Clavien classification of postoperative complications [38, 39] (Table 3). Assessment will be performed by the investigator or the designated sub-investigator.

**Table 3 Tab3:** Dindo–Clavien definition of postoperative complications [38]

Grade	Definition
I	Any deviation from the normal postoperative course without the need for pharmacological treatment or surgical, endoscopic or radiological intervention
	Allowed therapeutic regimens are: drugs as antiemetics, antipyretics, analgesics, diuretics, electrolytes and physiotherapy
	This grade also includes wound infections opened at the bedside
II	Requiring pharmacological treatment with drugs other than those allowed for grade I complications
	Blood transfusions and total parenteral nutrition are also included
III	Requiring surgical, endoscopic or radiological intervention
IIIa	Intervention, not under general anesthesia
IIIb	Intervention, under general anesthesia
IV	Life-threatening complication (including central nervous system complications)^a^ requiring intermediate care or intensive care unit management
IVa	Single organ dysfunction (including dialysis)
IVb	Multiorgan dysfunction
V	Death of a patient
Suffix ‘d’	If the patient suffers from a complication at the time of discharge (see examples in Table 1), the suffix ‘d’ (for ‘disability’) is added to the respective grade of complication. This label indicates the need for a follow-up to fully evaluate the complication.

^a^Brain haemorrhage, ischaemic stroke, subarachnoidal bleeding, but excluding transient ischaemic attacks

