#### Analysis of secondary endpoint measures

All secondary endpoints will be analyzed using descriptive statistical methods and comparisons between groups will be performed with the appropriate statistical tests. For comparisons of frequencies between groups, the chi-square test and, if appropriate, the Fisher exact test, will be used. As appropriate, Student’s *t* test, the Mann–Whitney U test or analysis of covariance (ANCOVA) will be employed for group comparisons of quantitative data. All tests will be two-sided at a significance level of 5 %.

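### The secondary endpoint on non-infectious wound complications is named broadly but coded as blister yes/no, with one fixed assessment at visit 3

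*Protocol article*

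**What the plan says.** - **Endpoint name.** The protocol article, Outcome measures, lists among the secondary endpoints the "Rate of wound complications other than wound infections in both groups". Nothing there limits it to one type of complication.
- **Coding rule.** In Interventions, Table 2, the row for other wound complications carries footnote c: "Documented as ‘yes’ if blister formation and ‘no’ otherwise". No other section widens or replaces this rule.
- **Timing.** That row is marked at visit 3 (postoperative day 5–7) and at the optional visit, which may fall at any time between visits 2 and 6. It is not marked at visits 4, 5 or 6.
- **Analysis.** Analysis of secondary endpoint measures states: "For comparisons of frequencies between groups, the chi-square test and, if appropriate, the Fisher exact test, will be used". Tests are two-sided at 5 %.

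**The concern.** The endpoint list promises a rate of non-infectious wound complications, and the data-capture rule delivers a rate of blisters. The second half of footnote c makes the rule exhaustive: blister formation is the sole condition for a yes, not one example among several.

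If the plan is followed as written, two groups will be compared on blister formation and the result will appear as a comparison of wound complications. A reader would take a null or adverse result as a statement about all non-infectious wound problems, which the data could not support. The loss occurs at data capture, so no later analysis of this item can recover complications recorded as no, or not asked about.

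**Working it through.** The protocol gives no expected rate for this endpoint, so there is no plan figure to reproduce. The check is a comparison of sections.

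**1. Name against rule.** The name covers every wound complication that is not an infection. The rule covers blisters. The two agree only if blisters are the sole non-infectious wound complication, which the document does not claim.

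**2. Schedule (Table 2).**

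| Item | Visit 3 | Visit 4 | Visit 5 | Visit 6 | Optional |
|---|---|---|---|---|---|
| Surgical site infection | × | × | × | × | × |
| Other wound complications | × | – | – | – | × |
| Wound pain | × | × | × | × | × |
| Reoperation | × | × | × | × | × |
| Adverse events (also visit 2) | × | × | × | × | × |

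Column positions are read from extracted text, but the neighbouring rows fit this reading. A blister first present after visit 3 enters the endpoint only if an optional visit takes place.

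**3. Where a non-blister event goes.**

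- *Deep dehiscence with symptoms.* Table 1 counts as infection the case where "A deep incision spontaneously dehisces or is deliberately opened by a surgeon when the patient has at least one of the following signs or symptoms". The list that follows there covers raised temperature and local pain or tenderness, and a culture-negative site is excepted. A culture-negative dehiscence that meets no other criterion in Table 1 is not an infection, and without a blister it is coded no here.
- *Event needing reoperation.* It appears in the reoperation endpoint, but not in this one.
- *Event needing surgical, endoscopic or radiological intervention.* It is grade III in Table 3, so it is recorded as an adverse event and compared in the Safety analysis, but it does not enter this endpoint.
- *Mild event.* Safety evaluation and reporting of adverse events exempts an event that is expected postoperatively and "that does not exceed grade I of the Dindo–Clavien classification of postoperative complications". An expected grade I wound event without a blister is therefore coded no here and need not be recorded as an adverse event. It may be recorded nowhere.

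**4. Can the effect be sized?** Only with assumed rates, none of which come from the document. Assume blisters in 1 % of controls and 5 % of the negative-pressure group, other complications at three assumed levels, and independence. Then:

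any complication = 1 − (1 − blister rate) × (1 − other rate)

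| Other, control v NPIT | Any, control | Any, NPIT | Difference, any | Difference, blister only |
|---|---|---|---|---|
| 5 % v 2.5 % | 1 − 0.99 × 0.95 = 5.95 % | 1 − 0.95 × 0.975 = 7.38 % | +1.43 points | +4 points |
| 10 % v 5 % | 1 − 0.99 × 0.90 = 10.90 % | 1 − 0.95 × 0.95 = 9.75 % | −1.15 points | +4 points |
| 15 % v 8 % | 1 − 0.99 × 0.85 = 15.85 % | 1 − 0.95 × 0.92 = 12.60 % | −3.25 points | +4 points |

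The blister-only difference stays fixed while the broader one changes sign with the assumptions. This shows that the two are different variables. It does not estimate what would happen in this trial.

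**The case against.** The strongest reply is that this is a label on one of seven secondary endpoints. Visit 3 falls at the end of the 5–7 days of device coverage, so a blister check then is a coherent tolerability measure, and the important non-infectious events are captured by other routes. The full protocol or the case record form may also record more than the article shows.

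Much of this stands. The blister item is sensible in itself, and the primary endpoint and the sample size are untouched. But none of the other routes feeds this endpoint, and the article does not merely omit detail: it states a rule that conflicts with its own endpoint list. If the case record form is broader, footnote c is wrong and still needs correcting.

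Four stronger readings are tempting, and the document does not support them:

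- *That dehiscence, seroma and haematoma count as no complication in the trial.* They would be coded no for this one variable; serious cases can surface as infection, reoperation or adverse event. Seroma and haematoma are not named in the protocol as components of this endpoint.
- *That anything first seen at visits 4 to 6 is recorded as no.* The item is not scheduled at those visits, which is different from being coded no, and a late blister can still enter through the optional visit.
- *That the endpoint can show harm but not benefit.* The protocol nowhere says that blisters are expected from the device, and its Risks section anticipates no additional risk.
- *That the coding hides a claimed benefit.* The Rationale says the devices were designed, among other aims, "to reduce tensile forces across the incision and to protect the incision from external contamination", but then calls the clinical benefit largely unclear. The benefit under test is fewer surgical site infections, and no hypothesis is stated for other wound complications.

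**Conclusion.** The point holds as an inconsistency between an endpoint's name and its only coding rule, made worse by a single fixed assessment. As written, the plan would report a blister rate, collected at visit 3 and at any optional visits, as the rate of non-infectious wound complications.

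The gap in the trial's records as a whole is mainly in expected wound events up to Dindo–Clavien grade I; more serious events are partly captured elsewhere. Neither the size nor the direction of any distortion follows from the document. The conclusion rests on reading footnote c literally and on the column positions in Table 2. It concerns a secondary endpoint only and should be settled before recruitment starts, because data not captured cannot be restored in the analysis.

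**What to change.** Make the name and the rule agree, in one of two ways:

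1. **Keep the broad endpoint.** Change footnote c so that yes means any non-infectious wound complication, with the type recorded and blisters reported separately. Mark the row at visits 3, 4, 5 and 6 and at the optional visit. The cost is a few case record form items at visits where a blinded assessor already documents surgical site infection; no visit is added.
2. **Keep the blister item.** Rename the endpoint as blister formation up to visit 3 or at an optional visit, in both Outcome measures and Table 2, and do not report it as wound complications. The cost is a change of wording, and the trial then has no endpoint for other non-infectious wound complications.

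The first serves the endpoint list as it stands. The second is enough if only local tolerability was meant.
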